### Plans for collection, laboratory evaluation, and storage of biological specimens for genetic or molecular analysis in this trial/future use {33}

See above in 26b. This study will not collect biological specimens for storage.

## Statistical methods

### Statistical methods for primary and secondary outcomes {20a}

#### Statistical analysis

Medication adherence will be assessed in individual patients by eCAP monitoring. Hypotheses will be tested at 6 months and 12 months.Tests are two-tailed at 5% level of significance. We compare group 1 patients to group 2 patients at baseline using, as appropriate, ANOVA-F-tests, chi-square tests, and non-parametric tests to assess equivalence of potentially confounding physiological and contextual patient characteristics. If substantive differences are found, they will be adjusted for in subsequent analyses by regression techniques, guided by the degree of dissimilarity rather than strict statistical significance [63]. Equivalence between the groups will be assessed on age, gender, education, race/ethnicity, use of statins, b-blockers, aspirin, and ACE1/ARB, blood sugar and lipid values, and team factors such physician experience.

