## Assignment of interventions: allocation

### Sequence generation {16a}

#### Randomization

We chose team-level assignment to unify all providers and patients at a team into a single intervention, minimizing risk of contamination. Seventeen teams from 12 clinics in 3 counties (with 4, 7, and 6 teams, respectively) agreed to participate in the trial. We first generated a uniformly distributed random variable (U) using a pseudo-random number generator in Stata and each team was allocated a random number. Then we stratified the teams by county, and the randomization procedure within each county followed these steps. In the county that had 1 team per clinic, the teams were sorted by U and the first half of the teams were assigned for group 1 and the second half for group 2. In the county that had 3 clinics with 2 teams and 1 clinic with 1 team, we sorted the teams within each clinic by their U values and in the 2-team clinics the first one was assigned to group 1 and the other to group 2; and the single-team clinic was randomly assigned to group 1 because U was less than 0.5 (which is a predetermined rule for assignment). Finally in the county with 3 teams in 1 clinic and 1 team in 1 clinic, all teams were sorted by U and the first 2 teams were assigned to group 1 and the last 2 teams were assigned to group 2. Overall, 9 teams were assigned to group 1 and 8 to group 2.

We chose this approach because it is realistic for providers and patients. This also helps the comparison of control and intervention groups to be more accurate because there is less chance of mixing between the two groups. In Michigan, FQHCs have similar numbers and types of providers (internal medicine, and family medicine) and nurse practitioners.

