##### Analysis of the primary and secondary outcomes

We adopt a regression-based approach to multivariable modeling that incorporates features of clustering of patients within the practice team and correlation over time in repeated assessments. Repeated measures ANOVA, or more apropos, generalized linear (mixed) models (GLMM) will be used [64]. Generally, outcomes are assessed at baseline and at 2 additional time-points 6 months and 12 months. By choice of link function connecting the expected patient outcome to covariates, GLMM can be applied to different types of outcomes (continuous, categorical, count, ordinal). They can incorporate random effects to capture serial correlation within patient measures, and clustering of patients within practice teams. Covariates are patient characteristics, some of which are time-invariant such as the aforementioned sociodemographic variables, and characteristics of the practice team. Key right-hand side variables in addition to the covariates are a single indicator for group, with control as referent, two indicators for time, with baseline as referent and group by time interactions. The GLMM allows us to formulate and test hypotheses on functions of the regression parameters: they include (i) point-in-time comparison between group 1 and group 2, (ii) time-averaged comparison between group 1 and group 2, (iii) within group comparison for change over time, and (iv) change in group 1 compared to the corresponding change in group 2 via difference-in-differences (DID). SAS Software (ver 9.4, Analytics 15.1 or higher) will be used for statistical analyses.

##### Analysis of the exploratory outcomes in Aim 3

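### The primary model's adjustment set is left to observed baseline dissimilarity with no threshold, alongside tests that ignore teams, and county is not a named model term

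*Protocol article*

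**What the plan says.** Under Statistical methods {20a}, Statistical analysis, the protocol compares group 1 and group 2 patients at baseline with "ANOVA-F-tests, chi-square tests, and non-parametric tests to assess equivalence of potentially confounding physiological and contextual patient characteristics". The rule for adjustment follows: "If substantive differences are found, they will be adjusted for in subsequent analyses by regression techniques". The same sentence ends by saying that this choice is to be "guided by the degree of dissimilarity rather than strict statistical significance". The characteristics to be compared are demographic variables, use of four drug classes, blood sugar, lipids and "team factors such physician experience". No size of difference is given that would count as substantive.

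Under Analysis of the primary and secondary outcomes, covariates are given as classes: "Covariates are patient characteristics, some of which are time-invariant such as the aforementioned sociodemographic variables, and characteristics of the practice team". The terms that are fixed are those for arm, time and their interaction: "Key right-hand side variables in addition to the covariates are a single indicator for group, with control as referent".

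Under Randomization, teams rather than patients were allocated: "Then we stratified the teams by county". The three counties had 4, 7 and 6 teams. In the seven-team county, the two teams of each two-team clinic were split between the arms. Neither county nor this pairing is named in the baseline list or among the model terms.

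**The concern.** There are four linked problems.

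- **The rule depends on the data.** Whether a covariate enters the primary model depends on the difference observed, judged without a stated cut-off. The Who will be blinded section says the researchers are not blinded. A primary model that is not fixed leaves room for choice that no reader can audit afterwards. The Moderators and mediators section adds a second data-dependent look, at how far the treatment coefficient moves when covariates are added.
- **The tests do not match the design.** The Design section requires outcome analyses to allow for intra-cluster correlation, and the outcome and cost analyses do so. The baseline comparison names ordinary tests and no such allowance, so normal variation between teams can look like imbalance.
- **The stated aim cannot be met.** A test of difference that fails to reject does not show equivalence, and no equivalence margin is given.
- **The randomisation stratum is not secured.** County shaped the allocation, but nothing commits the analysis to include it.

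At stake is the credibility of the primary estimate. The protocol states a rule here, so this is not detail left to the statistical analysis plan: a plan that followed the protocol would inherit the rule.

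**Working it through.** The protocol gives no figure for the baseline comparison, so there is none to reproduce. The check asks how often the screen would flag a covariate when there is no systematic difference between the arms.

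**Inputs from the protocol.** "Tests are two-tailed at 5% level of significance". From the Sample size section: 9 and 8 teams with at least 22 patients each, so 198 and 176 patients. This agrees with recruitment: 378/17 = 22.2 per team. The only ICC given is 0.002, and it is for the outcome.

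**Assumed.** The ICCs of the baseline covariates are not given; 0.002 to 0.10 is shown. A factor constant within team has ICC 1. A cut-off of 0.2 for the standardised difference stands in for the unstated threshold.

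**Formulas**

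- Design effect: DE = 1 + (22 − 1) × ICC.
- False-flag rate of a 5% test that ignores teams: 2 × [1 − Φ(1.96/√DE)].
- Standard error of a standardised difference: √[DE × (1/198 + 1/176)] = 0.1036 × √DE. Chance of exceeding 0.2 in size: 2 × [1 − Φ(0.2/SE)].

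Example at ICC 0.05: DE = 1 + 21 × 0.05 = 2.05; 1.96/√2.05 = 1.369; false-flag rate 17.1%.

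| Covariate ICC | DE | False-flag rate, formula | Simulated (20,000 runs) | Standardised difference above 0.2 |
|---|---|---|---|---|
| 0.002 | 1.042 | 5.5% | 5.3% | 5.9% |
| 0.02 | 1.42 | 10.0% | 9.9% | 10.5% |
| 0.05 | 2.05 | 17.1% | 17.5% | 17.8% |
| 0.10 | 3.10 | 26.6% | 26.8% | 27.3% |
| 1 (constant within team) | 22 | 67.6% | 69.4% | 68.1% |

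With no clustering, the last column would be 5.4%. A test on team means held between 4.9% and 5.2% at every ICC simulated.

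**Effect of selection on the outcome test.** A simulation of 4,000 runs per setting used one covariate (correlation 0.4 with the outcome), an outcome ICC of 0.002 and no treatment effect. It adjusted only when the test ignoring teams gave p < 0.05.

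| Covariate ICC | Type I error, pre-specified adjustment | Type I error, selected adjustment |
|---|---|---|
| 0.02 | 4.5% | 3.9% |
| 0.05 | 5.1% | 4.3% |
| 0.10 | 4.9% | 3.3% |

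Selection made the test slightly conservative.

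**Effect on the difference-in-differences (DID).** A linear random-intercept simulation (17 teams of 22, covariate ICC 0.05, a county effect built in, 200 runs) compared the 12-month DID with and without the covariate and county. With complete data, estimate and standard error were identical, because time-invariant main effects cancel from within-patient change. With about 13% covariate-dependent dropout, the estimate moved with an SD of 0.009 against a standard error of 0.129, and the standard error changed by 0.3%.

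**The case against.** A reader might infer four stronger things that the documents do not support.

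- **That p-values choose the covariates.** The protocol says that the degree of dissimilarity guides the choice, not strict significance. This stands, and false flags are not automatically adjusted for. It does not rescue the rule: the size of an observed difference is inflated by clustering in the same way, as the last column of the first table shows.
- **That the rule inflates the false-positive rate.** The simulation shows no inflation.
- **That covariates are chosen with outcomes in view.** The protocol says that researchers know the arm. It does not say that the baseline comparison waits for outcome data.
- **That leaving out county costs precision throughout.** The primary hypotheses are DIDs with baseline as a response. In a linear model with complete data, county cancels from them.

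Other points also carry weight. At the protocol's own ICC of 0.002, mis-flagging is trivial. The figure of about 68% needs a factor constant within team and a patient-level comparison; the protocol does not say how team factors are compared, and experience may vary among a team's providers. The covariate class for practice-team characteristics could include county, though it does not say so. Finally, the Implementation section says clinical staff were told the allocation before patients were enrolled, so recruitment could differ between arms for real. That is a good reason to describe baseline data and to adjust for prognostic variables. It is a reason to choose them beforehand, not to let the observed differences choose them.

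**Conclusion.** The point holds in a limited form and should be acted on. The protocol lets observed baseline dissimilarity, without a threshold, decide the adjustment set. It accompanies this with tests that ignore teams and cannot show equivalence, and it does not name county as a model term. The harm is a primary model not fixed in advance in an open-label trial, with adjustment driven partly by ordinary between-team variation.

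The size depends on covariate ICCs that the protocol does not give: negligible near 0.002, about double to more than triple the nominal 5% at 0.02 to 0.05, and dominant for factors constant within team and compared at patient level. The practical effect falls mainly on the point-in-time contrasts and on the beta regression for the medication adherence index. There the logit link prevents exact cancellation, and the baseline value is only a proxy because eCAP data do not exist before enrolment. A linear-model DID would be little affected.

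**What to change.** Replace the baseline-testing and conditional-adjustment sentences with three commitments:

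1. Report baseline characteristics by arm descriptively, with standardised differences and without tests that ignore teams. Show team-level factors at team level.
2. Before any outcome analysis, fix the covariates of the primary model: county, plus a short list of prognostic variables already collected, such as age, sex and baseline HbA1c. Reflect the within-clinic pairing in the county where it was used, at least in a sensitivity analysis. Baseline ARMS may be a covariate in the eCAP adherence model only. In the ARMS model it is already a response and would be used twice.
3. Treat adjustment for any further observed imbalance, and the look at changes in the treatment coefficient, as sensitivity analysis.

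The cost is wording. No new data are needed and no figure in the protocol changes. With 17 teams in two arms there are about 17 − 2 = 15 team-level degrees of freedom. Three counties use 2 of them, leaving about 13.

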##### Analysis of the primary and secondary outcomes

We adopt a regression-based approach to multivariable modeling that incorporates features of clustering of patients within the practice team and correlation over time in repeated assessments. Repeated measures ANOVA, or more apropos, generalized linear (mixed) models (GLMM) will be used [64]. Generally, outcomes are assessed at baseline and at 2 additional time-points 6 months and 12 months. By choice of link function connecting the expected patient outcome to covariates, GLMM can be applied to different types of outcomes (continuous, categorical, count, ordinal). They can incorporate random effects to capture serial correlation within patient measures, and clustering of patients within practice teams. Covariates are patient characteristics, some of which are time-invariant such as the aforementioned sociodemographic variables, and characteristics of the practice team. Key right-hand side variables in addition to the covariates are a single indicator for group, with control as referent, two indicators for time, with baseline as referent and group by time interactions. The GLMM allows us to formulate and test hypotheses on functions of the regression parameters: they include (i) point-in-time comparison between group 1 and group 2, (ii) time-averaged comparison between group 1 and group 2, (iii) within group comparison for change over time, and (iv) change in group 1 compared to the corresponding change in group 2 via difference-in-differences (DID). SAS Software (ver 9.4, Analytics 15.1 or higher) will be used for statistical analyses.

##### Analysis of the exploratory outcomes in Aim 3

Cost analysis will provide estimates for the value of resources used by each patient [65]. The value of resources not directly related to patient interaction, such as training costs and non-labor costs, will be allocated evenly across the intervention groups. Direct medical costs include expenditures for medical services and products usually paid for by the health system and consumer, including intervention costs (group visits, Texting), cost of medical care outside the interventions (use of hospital, emergency room, urgent care, outpatient visits, and prescription medications), and IT support (text messaging support). Direct non-medical costs include time and transportation to and from clinic visits and care provided by family members. Total cost per group at the end of the study will be computed by summing the costs for each patient. Mean cost per group will be calculated by dividing the total cost by the number of patients in each group. Research costs will not be included. Cost analysis will consider the perspective of the health system (FQHCs) and the consumer (patient). For costs analyses, we will follow the guidelines of the International Society for Pharmacoeconomics and Outcomes Research (ISPOR) Task Force on Good RCT-CEA Research Practices and will use the sample size determined for primary outcome in Aim 1 for cost analyses [66, 67]. Unit of analysis will be the patient [68]. All costs will be discounted to the base year according to time elapsed since randomization [69]. Distribution of cost data will be examined, and the differences in costs between study groups will be tested accounting for the nesting of patients within team clusters. Generalized linear models for Poisson distribution, or zero-inflated Poisson or negative Binomial model for counts of different healthcare utilizations will be used to compare the groups. Each type of health service use (e.g., hospitalizations, emergency room visits) will be analyzed separately. Two-part models for expenditures will typically be adopted to account for zero-expenditure for some individuals [70].

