#### Intervention description {11a}

Patients in either the intervention or control group will receive medical treatment-as-usual from the participating clinics, consisting of diabetes care, usual preventive care, and other medical treatment as needed (Table 1).

**Table 1 Tab1:** Intervention components

	Physician and staff education model for all intervention groups	
	GROUP 1 PAI + Texting	GROUP 2 Texting only
**Baseline visit**	**Group visit** **• Office-GAP PAI** **• Way2Health Texting program** **• BP Check** **• Surveys and checklist use**	**Group visit** **• Way2Health Texting program Only** **• BP Check** **• Complete Surveys**
**PAI (group 1)**	**• Baseline evaluation and patients complete all study questionnaires** **• Introduction to CVD/DM and lifestyle changes** **• Discussion of benefits of using each cardiac/diabetes medication** **• Discussion of goal setting, shared decision-making, and patient engagement** **• Review of patients’ medications and completion of the** ***Office-GAP agreement*** **• Review of ACP Booklet** ***Living with Diabetes & Medication Adherence video*** **• Pre and post evaluation of the group visit**	
**Texting (Care4Life) (groups 1 and 2)**	**•** ***Medication Adherence Intervention*****:** **Way2Health sends educational messages and quizzes on medication and adherence** **User responds to quiz** **•** ***DM Self-Management*** **Way2Health sends educational messages and quizzes on DM self-management** **User responds to quiz** **•** ***Blood Sugar Control Intervention*** **Way2Health sends educational messages about healthy blood sugar** **Way2Health sends blood sugar testing reminders** **User enters blood sugar readings and receives feedback on goals** **•** ***Blood Pressure Control Intervention*** **Way2Health sends educational messages about healthy BP** **Way2Health sends reminders to check and record BP** **User enters BP readings and receives feedback on goals** **•** ***Appointment Attendance Intervention*** **Way2Health sends appointment reminders** **User confirms appointment or reschedules**	
**6 and 12 months**	**-PAI Decision checklist** **-BP Check** **-Review of texting use** **- Surveys and exit interviews**	**-BP Check** **- Review of Texting use** **-Follow-up surveys** **-Exit Interviews**

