##### Office-GAP follow-up visit with providers

The Office-GAP Checklist is the core tool of our SDM intervention. A one-page checklist, this SDM tool outlines all evidence-based medications for secondary prevention of CVD in T2DM patients. It is an in-consultation decision support tool that helps engage the patient and provider to encourage and enhance an SDM process via discussion of medication and secondary prevention/lifestyle changes during an office visit. In this study, the Office-GAP Checklist will be completed by the physician with direct patient involvement during the office visits at 0–1, 3, 6, 9, and 12 months. Only group 1 patients will use this checklist during their office visits.

The Office-GAP Checklist also serves as a physician reminder at the point of care, because the physician records a checkmark for each medication: “Yes” (if patient is on the medication), “No” (if patient is not), or “Does not apply to me because….” A reason for exclusion of a medication is also provided (patient is not eligible for the medication, has a contraindication to its use, or the patient and physician have identified an alternative due to side effect or cost concerns). Details about the next appointment and any secondary prevention plan changes are also listed on the form. At the end of the visit, both patient and physician sign the form to confirm that they have reviewed the checklist. The patient receives a copy of the checklist to take home and a copy is retained in the patient record. All providers in the intervention teams receive a brief physician education in Office-GAP tool use and communication skills.

Educational tool literacy standards: Office-GAP has been rigorously adapted for use with low health literacy patients. All study materials are grade 6 reading level.

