##### Provider and practice staff training

All intervention providers will participate in an interactive orientation which we have shown to promote behavioral change among health professionals. Providers will be asked to give their consent to participate in the study during this session. Provider/Staff Educational module: The training session is 60–90 min [22]. The session is scheduled multiple times to meet providers’ needs. In our pilot Office-GAP study, we achieved 100% participation by providers. The training module, facilitated by PI and co-investigators, includes (1) brief presentations on effectiveness and cost-effectiveness of medical therapy and behavior changes in management of T2DM, blood pressure, and heart disease; (2) a hands-on practice session for providers to elicit patients’ preferences and values; (3) an introduction to the Office-Gap Checklist and best practices for using it during a patient encounter; and (4) review of the Smith evidence-based patient-centered method for establishing trust, communicating clearly, and engaging in goal-setting with patients [22]. Providers will have a chance to practice skills using Braddock [23] and Elwyn’s [24]) approach to role-playing to model office visits; and (5) a complete pre-and post-training survey (before and after the training session) to determine provider attitudes about the use of DSTs, SDM, and mHealth in their practice and an end of study semi-structured interview.

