##### Cost and healthcare utilization

The Micro-costing Questionnaire will be used to collect data from the expense report, including cost-generating events not directly linked to a specific patient, to calculate total labor expenses (e.g., training costs), and non-labor expenses (e.g., supplies, educational materials, and administrative overhead) utilized by each group in the study. Cost-generating events will include (1) training providers to promote behavioral change, (2) distributing DSTs and educational materials, (3) providing continued technical support to providers and patients in text messaging use, and (4) administrative overhead for FQHCs, if applicable. The Health Services Utilization Form was developed and tested in a prior trial and captures health services utilization and patient out-of-pocket expense [78]. It gathers self-reported number of times the patient visits a specialist (e.g., dietitian, cardiologist), emergency room/urgent care center/hospital for DM or heart problems, and co-payment, deductibles, and other out-of-pocket expenses for DM or heart problems during the study period. Occurrences of healthcare utilization will be valued using the average cost in the Medical Expenditure Panel Survey for similar patients [79].

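### The even split of training and non-labor costs between arms removes a group 1 cost from the exploratory Aim 3 cost difference

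*Protocol article*

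**What the plan says.** All references are to the protocol article.

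- **Allocation rule** (Statistical methods {20a}, Analysis of the exploratory outcomes in Aim 3): resources without a direct link to a patient, "such as training costs and non-labor costs, will be allocated evenly across the intervention groups". Group visits and texting are listed separately as direct intervention costs. Mean cost per group is the group's total divided by its number of patients.
- **Who is trained** (Office-GAP follow-up visit with providers): "All providers in the intervention teams receive a brief physician education in Office-GAP tool use and communication skills". The same section restricts checklist use to group 1 patients.
- **The training** (Provider and practice staff training): "All intervention providers will participate in an interactive orientation". On length: "The training session is 60–90 min", scheduled several times. Content includes "an introduction to the Office-Gap Checklist and best practices for using it during a patient encounter".
- **Arm labels**: the Abstract calls group 1 the intervention and group 2 the control. Trial design {8} calls both arms intervention groups.
- **Table 1** (Intervention description {11a}) carries a header over both arms: "Physician and staff education model for all intervention groups".
- **Cost data** (Cost and healthcare utilization): the Micro-costing Questionnaire totals labor expenses, such as training, and non-labor expenses, such as supplies and educational materials, "utilized by each group in the study". Provider training and the distribution of decision tools and materials are two of the four listed cost-generating events.

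**The concern.** Aim 3 asks whether costs differ between groups 1 and 2. A cost shared equally by both arms cannot contribute to that difference, whatever its size. The rule is harmless for resources that both arms use equally. The checklist training is different: the article places it in group 1, and only group 1 uses the tool it teaches. Applying the rule to that training charges about half of it to teams that did not use it.

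The rule also discards information the trial plans to hold, because the questionnaire records these expenses by group.

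At stake is the incremental cost reported to health centers that are considering adoption. The analysis takes the health center's perspective, the Discussion announces an evaluation of cost-effectiveness, and Limitations reports that rising staff turnover has meant training new providers. Training is therefore a cost an adopting center would meet, and possibly more than once.

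**Working it through.** The article gives no cost figure, so there is no stated result to reproduce. The check is how a cost passes through the rule.

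**Inputs**
- Teams and patients (Sample size {14}): 9 and 8 teams with at least 22 patients each, so n1 = 9 × 22 = 198 and n2 = 8 × 22 = 176.
- T: total cost of provider training, decision tools and materials used only by group 1. Its value is not in the article and is an assumption below.

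**Contribution of T to the mean cost difference (group 1 minus group 2)**

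1. Charged to the group that used it: T/n1 = T/198 = 0.00505T.
2. Split evenly per patient: T/374 - T/374 = 0.
3. Split evenly per team: (9T/17)/198 - (8T/17)/176 = T/374 - T/374 = 0.
4. Halved by arm: (T/2)/198 - (T/2)/176 = T/396 - T/352 = -T/3168 = -0.00032T.

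The understatement is T/198 under lines 2 and 3. Under line 4 it is T/198 + T/3168 = 17T/3168 = 0.00537T.

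**Illustration with assumed T**

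| Assumed T ($) | Charged to group 1 | Per patient or per team | Halved by arm | Understatement per patient |
|---|---|---|---|---|
| 5,000 | 25.25 | 0 | -1.58 | 25.25 to 26.83 |
| 20,000 | 101.01 | 0 | -6.31 | 101.01 to 107.32 |
| 50,000 | 252.53 | 0 | -15.78 | 252.53 to 268.31 |

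With the 320 evaluable patients divided 9:8 (about 169 and 151), T/n1 becomes 29.51, 118.06 and 295.14 for the same three values.

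**When the even split would be right.** Let s be the share of T that group 2 actually uses. The correct contribution is (1 - s)T/198 - sT/176. This is zero at s = 8/17, and equals the halved-by-arm result at s = 1/2. The rule is therefore accurate only for resources that both arms use about equally, and a checklist module used only by group 1 has s = 0.

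**The case against.** **The rule might mean something else.** The cost paragraph opens by saying it values the resources each patient uses, so a cost without a patient link has to be spread somehow. Read with the micro-costing section, the plan could be to total these costs by group and then spread them evenly over that group's own patients. That would remove the problem, but it strains the sentence, which speaks of groups in the plural, the term Trial design {8} uses for the two arms. The two sections at least need reconciling.

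**Control providers may be trained too.** The Table 1 header covers both arms. The eligibility section includes every provider in the participating clinics. The only provider consent step described takes place at the training session. If both arms attended the same training, an even split would be about right for it. This leaves real doubt about general education for group 2. It does not rescue the rule for the checklist module, which only group 1 uses.

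**The amount may be modest.** Group visits, which carry the Office-GAP patient session, and texting are charged directly and stay in the difference. The investigators facilitate the training and research costs are excluded, so part of T may not count. Some non-labor costs are shared, and splitting them does no harm. All of this stands and limits the size of the point, though not its direction.

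**Stronger readings a reader might infer.** One is that the rule omits a main cost of the intervention, but no cost figure supports that. Another is that the control arm will look costlier. That arises only if T is halved by arm, and then only by T/3168. A third is that the Table 1 header shows control providers were trained in shared decision-making, which would dilute the primary contrast. The header does not say what that education contains, so this is speculation.

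**Conclusion.** The point holds in a limited form. As written, the allocation rule contradicts the sections that place Office-GAP provider training in group 1 and the section that collects these expenses by group. It removes a listed group 1 cost from the Aim 3 difference, which is understated by T/198 per patient, or by 17T/3168 if the cost is halved by arm. The amount cannot be stated because T is unknown; the dollar figures above only illustrate the scale.

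For any positive cost used only by group 1, the error makes Office-GAP + Texting look cheaper. This rests on two readings: that the rule splits costs between the arms, and that the checklist training serves group 1 alone. Both are the more natural readings of the text. Aim 3 is exploratory, and no primary or secondary outcome or power figure depends on the rule.

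**What to change.** 1. Replace the even-split rule. Charge provider training, decision-support tools and educational materials to the group that used them, taking the amounts from the group-level Micro-costing Questionnaire.
2. Split only overhead that both arms share, and do so per patient so that unequal group sizes do not create a difference.
3. Reconcile the Table 1 header with the two sections on provider training by stating what training, if any, group 2 providers receive. Charge whatever they do receive to group 2.
4. Leave group visits and texting as direct intervention costs, as now planned.

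The cost is one changed allocation rule and one clarified table header. The group-level expenses are already to be collected, so no new data are needed. The downside is that Office-GAP + Texting will look somewhat more expensive in the Aim 3 comparison.
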